### Study endpoints

This trial aims to assess the efficacy and safety of hUC-MSC PLEB001 in patients with grade II–IV steroid-refractory aGVHD. The primary endpoint is the overall response rate (ORR) at day 28, which is defined as the proportion of patients achieving a CR or PR without the use of additional systemic therapies for aGVHD. The secondary endpoints include the CR rate at day 28, ORR at day 56, CR rate at day 56, durable ORR at day 56, DCR, OS, and Eastern Cooperative Oncology Group (ECOG) score. The safety endpoints include adverse events (AEs), serious adverse events (SAEs), and infusion toxicity (Table 2).

**Table 2 Tab2:** Study endpoints

Aim	Indicator
Primary endpoint	ORR at day 28
Secondary endpoints	CR at day 28, day 56
	ORR at day 56
	Durable ORR at day 56
	DCR within day 100
	OS at day 100, day 180
	ECOG score at day 28, day 56, day 100
Safety endpoints	AE/SAE at day 180
	infusion toxicity at day 14

1. Complete remission (CR): absence of any aGVHD-related symptoms

2. Partial remission (PR): an improvement in severity of at least 1 stage in all initial organs without further deterioration of other organs

3. No response (NR): the absence of improvement or deterioration of symptoms in any organ or death

4. Progressive disease (PD): a deterioration in the severity of at least 1 stage in a single organ with or without improvement in other organs

5. Overall response rate (ORR) = CR + PR

6. Durable ORR: the percentage of subjects who achieve CR + PR on day 28 and remain CR + PR on day 56

7. Durable complete response (DCR): complete resolution of aGVHD symptoms for at least 28 days within 100 days after the first infusion

8. Infusion toxicity includes fever, phlebitis, headache, dizziness, nausea, chest pain, shortness of breath, transient pulmonary edema, allergic reaction, skin rash, injection site pruritus, etc.

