### Sample size

This study is an exploratory study, so the sample size will not take into account the power associated with statistical hypotheses. Forty randomized subjects in each group will be included in the statistical analysis. Assuming a 20% dropout rate, we plan to enroll 96 subjects (48 in each group).

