### Statistical analysis

All analyses will be carried out according to a predetermined statistical analysis plan by utilizing SAS 9.4. Two-tailed tests will be used for most statistical tests, and a *p* value of less than 0.05 will be considered statistically significant. Comparisons between groups for quantitative data will be performed by the independent samples *t* test or Wilcoxon rank sum test. Comparisons between groups of categorical data will be performed by the chi-square test or Fisher’s precision probability test. Comparisons between groups of ranked data will be performed by the Wilcoxon rank sum test or CMH test.

The full analysis set (FAS) is the set of subjects identified according to the intention-to-treat (ITT) principle. It includes all patients who have received at least one dose of study treatment after randomization. The per-protocol set (PPS) consists of the subjects in the FAS who meet the requirements of the trial and are in good compliance. The formula for calculating the adherence of subjects is as follows: adherence rate = (actual infusion dose during follow-up/planned infusion dose) × 100%. Good compliance is defined as ≥ 80% adherence rate. The safety set (SS) includes all patients who received at least one dose of study treatment. The primary and secondary efficacy analyses will be based on both the FAS and PPS. Subjects who present with protocol nonadherence will be analyzed in the FAS and SS.

Adverse events, laboratory tests, symptoms, signs, and the association between adverse events and the trial drug are presented in the form of a table.

The missing values of the primary endpoint will be processed by worst observation carried forward (WOCF). The other missing values will be analyzed on the actual observed data.

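### The listed tests state no baseline adjustment for ECOG at days 28, 56 and 100, although ECOG is measured at screening

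*Protocol article*

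**What the plan says.** Table 2 of the Protocol article (Study endpoints) lists among the secondary endpoints "ECOG score at day 28, day 56, day 100". In Table 1 the ECOG row is marked at screening and at the day 28, 56 and 100 visits. Exclusion criterion vii removes only scores above 3, so patients may enter with ECOG 0, 1, 2 or 3.

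The Statistical analysis section assigns tests by type of data. For ordered data: "Comparisons between groups of ranked data will be performed by the Wilcoxon rank sum test or CMH test". For continuous data: "Comparisons between groups for quantitative data will be performed by the independent samples *t* test or Wilcoxon rank sum test". It mentions no covariate, change score, model or CMH stratum, and it does not say whether ECOG counts as ranked or quantitative. The same section says "All analyses will be carried out according to a predetermined statistical analysis plan by utilizing SAS 9.4"; that plan is not shown. On the error rate it says "Two-tailed tests will be used for most statistical tests, and a *p* value of less than 0.05 will be considered statistically significant".

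The Sample size section calls the study exploratory, says that "the sample size will not take into account the power associated with statistical hypotheses", and plans that "Forty randomized subjects in each group will be included in the statistical analysis". The Randomization section describes blocks by center and states no stratification by ECOG.

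**The concern.** Every randomized patient should have a screening value on the same scale as this outcome, and the eligible range covers four levels. A two-sample Wilcoxon or t test on the follow-up score ignores that value. A patient who enters at 3 and improves to 2 then ranks below one who enters at 0 and worsens to 1.

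Two things are at stake. Any part of the follow-up variation that screening ECOG predicts stays in the error term. And if the arms happen to differ at screening, which the randomization as described does not prevent, that difference carries into all three comparisons. With about 40 patients per arm and no power calculation behind the trial, precision is scarce, and the data needed to recover some of it are already being collected.

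**Working it through.** **Inputs from the article.** 40 analysed per arm; two-sided 5% level; ECOG at screening 0 to 3. The article's own derived figure reproduces: 40 × 1.20 = 48 per arm, 96 in total. It states no power, effect size or correlation for ECOG, so there is no ECOG figure to reproduce.

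**Assumed.** The correlation ρ between screening and follow-up ECOG (0, 0.3, 0.5, 0.7) and a treatment difference of 0.5 or 0.6 SD.

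**Step 1: variance.** Adjusting for baseline multiplies the variance by 1 − ρ². The equivalent unadjusted size is 40/(1 − ρ²) per arm. For a 0.5 SD difference, power is approximately Φ(0.5/√[(2/40)(1 − ρ²)] − 1.96).

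| ρ | 1 − ρ² | Equivalent n per arm | Power |
|---|---|---|---|
| 0 (unadjusted) | 1 | 40 | 61% |
| 0.3 | 0.91 | 44 | 65% |
| 0.5 | 0.75 | 53 | 73% |
| 0.7 | 0.51 | 78 | 88% |

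**Step 2: ordinal scores.** Step 1 treats ECOG as continuous, which flatters the gain. Simulation used correlated latent normal values cut to four screening levels (0 to 3) and five follow-up levels (0 to 4), 40 per arm, with 4,000 runs per setting at 0.5 SD and 3,000 at 0.6 SD. The stratified test ranks patients within screening ECOG level (CMH/van Elteren type). Rank ANCOVA compares residuals of follow-up ranks regressed on screening ranks.

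| Shift | ρ | Wilcoxon | Stratified by screening ECOG | Rank ANCOVA |
|---|---|---|---|---|
| 0.5 SD | 0 | 54% | 52% | 54% |
| 0.5 SD | 0.3 | 55% | 56% | 58% |
| 0.5 SD | 0.5 | 55% | 62% | 63% |
| 0.5 SD | 0.7 | 55% | 75% | 76% |
| 0.6 SD | 0 | 69% | 66% | 68% |
| 0.6 SD | 0.3 | 71% | 72% | 73% |
| 0.6 SD | 0.5 | 69% | 77% | 78% |
| 0.6 SD | 0.7 | 69% | 87% | 88% |

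Stratifying gains about 1 point at ρ = 0.3, 7 to 8 at 0.5 and 18 to 20 at 0.7, and costs 2 to 3 points at ρ = 0.

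**Step 3: level of the test.** With no treatment effect, the unadjusted rank test rejected in 4.8% to 5.2% of runs. It keeps its nominal level.

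**Step 4: chance imbalance.** The SD of the difference in mean screening score is √(2/40) = 0.22 SD. An imbalance of two such SDs shifts the unadjusted contrast by ρ × 2 × 0.2236, which is 0.13, 0.22 and 0.31 SD at ρ = 0.3, 0.5 and 0.7. Given that imbalance, the type I error is 1 − Φ[(1.96 − 2ρ)/√(1 − ρ²)] + Φ[(−1.96 − 2ρ)/√(1 − ρ²)], which is 8%, 13% and 22%. For a one-SD imbalance it is 5.0%, 4.8% and 3.9%. These are conditional figures; averaged over randomizations they come back to the 5% in step 3.

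**Step 5: less favorable settings.** With 60% to 70% of patients in one screening level, the stratified gain at ρ = 0.5 falls to about 5 to 6 points, and at 0.3 it is under 1. With an assumed 25 observed per arm, stratifying loses about 1 point at ρ = 0.3 and gains 2 to 4 at 0.5. Smaller numbers are plausible because missing secondary outcomes are left as observed data only. None of the simulations models deaths.

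**The case against.** A reader might infer that the plan fixes an unadjusted test for ECOG. The article does not say that. Its test list is generic, assigns nothing to ECOG, and does not say whether a test would be applied to the follow-up score or to the change from screening. The ranked-data sentence also offers the Cochran–Mantel–Haenszel test, which can be stratified by screening ECOG. The remedy is therefore already within the listed methods, and what is lacking is the stratum.

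A reader might also infer bias. That is not supported either: randomization balances screening ECOG in expectation, and the unadjusted test holds its 5% level. The patient who goes from 3 to 2 shows no error in the plan, because Table 2 defines the endpoint as the score on the day, not the change.

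The strongest objection is that covariates and strata for one secondary endpoint are normally set in the statistical analysis plan, which exists and is not shown. Its silence here is not by itself a fault. The gain also rests wholly on an assumed correlation, which may be weak from screening to day 100, and the trial is exploratory.

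All of this stands as a limit on the point. It does not remove it: the article does name tests, and two of the three it offers for such data, Wilcoxon and t, make no use of screening ECOG when applied to the follow-up score.

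**Conclusion.** The point holds as a minor, optional improvement to a secondary analysis. The stated methods include no baseline adjustment for ECOG and leave its test open, although a baseline value is collected. The consequence is possible loss of precision and exposure to chance imbalance; the validity of the comparison is not in question.

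At 40 per arm the loss in power is negligible if the correlation is 0.3, about 6 to 8 points if it is 0.5, and about 18 to 20 if it is 0.7. The correlation, the treatment difference and the spread of scores are assumptions, and fewer observed patients make the gain smaller. No conclusion on the primary endpoint is affected.

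**What to change.** Before unblinding, state in the analysis plan which test applies to ECOG and how the screening score enters. Suggested wording: *ECOG at days 28, 56 and 100 will each be compared between arms with screening ECOG as a covariate (rank ANCOVA or a proportional-odds model). The unadjusted Wilcoxon test will be reported as a sensitivity analysis.* The alternative that stays within the listed tests is the CMH row-mean-score test stratified by screening ECOG, with sparse levels pooled by a rule set in advance.

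The cost is one extra analysis, with no new data or visits. If screening ECOG turned out to be unrelated to later ECOG, the stratified version would lose about 2 to 3 power points; rank ANCOVA lost essentially nothing in the same setting, which favors the covariate form. The proportional-odds model was not simulated. If the statistical analysis plan already specifies such an adjustment, the sponsor need only confirm it.

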Abdominal ultrasound scan^a^		**X**									**X**									**X**				
Th17 and Treg count (prior to MSC infusion)			**X**				**X**				**X**									**X**				
CEA, CA125, CA199, AFP^a^		**X**									**X**									**X**				
X-ray or CT of chest		**X**									**X**									**X**				
Gastrointestinal examination		**X**		**X**	**X**		**X**		**X**		**X**		**X**		**X**		**X**			**X**	**X**	**X**		
Cutaneous examination		**X**		**X**	**X**		**X**		**X**		**X**		**X**		**X**		**X**			**X**	**X**	**X**		
aGVHD evaluation^1^		**X**		**X**	**X**		**X**		**X**		**X**		**X**		**X**		**X**			**X**	**X**	**X**		
ECOG score		**X**									**X**									**X**		**X**		
Pregnancy test( for female of child bearing potential)		**X**									**X**									**X**				
SaO2/SAT^2^		**X**	**X**	**X**	**X**	**X**	**X**	**X**	**X**	**X**		**X**	**X**	**X**	**X**	**X**	**X**	**X**	**X**					
Inclusion/exclusion criteria		**X**																						
Intervention			**X**	**X**	**X**	**X**	**X**	**X**	**X**	**X**		**X**	**X**	**X**	**X**	**X**	**X**	**X**	**X**					
AEs			**X**	**X**	**X**	**X**	**X**	**X**	**X**	**X**	**X**	**X**	**X**	**X**	**X**	**X**	**X**	**X**	**X**	**X**	**X**	**X**	**X**	
Concomitant disease and medication		**X**	**X**	**X**	**X**	**X**	**X**	**X**	**X**	**X**	**X**	**X**	**X**	**X**	**X**	**X**	**X**	**X**	**X**	**X**	**X**	**X**	**X**	
Medical recording of aGVHD after investigational product																					**X**	**X**	**X**	
Imaging of secondary tumors																						**X**	**X**	**X**
Survival status			**X**	**X**	**X**	**X**	**X**	**X**	**X**	**X**	**X**	**X**	**X**	**X**	**X**	**X**	**X**	**X**	**X**	**X**	**X**	**X**	**X**	**X**

Subjects who withdraw from the trial should be assessed according to visit 19

Detailed information about the test items is shown in the clinical trial protocol V6.0, which could be provided by the trial sponsor

1. According to the modified Glucksberg criteria

2. Monitoring with a pulse oximeter at least 30 min before MSC infusion to 2 h after infusion

^a^Test results prior to randomization are acceptable during the screening period, and the exact time limits are described in the clinical trial protocol V6.0

Subjects who deviate from intervention protocols or the follow-up schedule of assessments will follow the same calendar as those with good compliance, except adherence assessment.

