Participants may withdraw from the study for any reason at any time. Investigators will make the best effort to evaluate patients based on visit 19 before they withdraw from the trial. Detailed reasons for withdrawal, concomitant medications, and adverse events will be recorded to obtain safety data for those who withdraw consent or are lost to follow-up.

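### WOCF for a missing day-28 response can, on its natural reading, credit responders who were not assessed at day 28, and the primary ORR then depends on whether the screening stage counts as an observation

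*Protocol article*

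**What the plan says.** All references are to the protocol article.

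- **Missing-data rule (Statistical analysis).** "The missing values of the primary endpoint will be processed by worst observation carried forward (WOCF". The section does not say which observations enter the comparison. All other missing data are left as observed.
- **Primary endpoint (Study endpoints).** ORR at day 28 is "the proportion of patients achieving a CR or PR without the use of additional systemic therapies for aGVHD". The notes to Table 2 define PR as "an improvement in severity of at least 1 stage in all initial organs without further deterioration of other organs" and NR as "the absence of improvement or deterioration of symptoms in any organ or death". Death before day 28 is therefore a non-response, not a missing value.
- **Assessment times (Table 1).** aGVHD is evaluated at screening, then on days 4, 8, 15, 22 and 28 (each ±1). There is no evaluation on day 1.
- **Full analysis set (Statistical analysis).** "It includes all patients who have received at least one dose of study treatment after randomization". No post-baseline assessment is required.
- **Withdrawal.** A note to Table 1 states: "Subjects who withdraw from the trial should be assessed according to visit 19". That visit includes an aGVHD evaluation and is scheduled for day 56. The text after the table is softer: "Investigators will make the best effort to evaluate patients based on visit 19 before they withdraw from the trial".

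**The concern.** WOCF is usually chosen as a conservative rule for a measurement followed over time. Here it is applied to a response category at one fixed day. The category exists only relative to the starting organ stages, so the worst observation is most naturally the worst category seen after baseline. A patient who leaves early while in response then has nothing but responses to carry forward, and becomes a day-28 success with no day-28 evidence.

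The rule may also leave a treated patient without a value, because one dose is enough to enter the full analysis set while the first scheduled post-baseline reading is on day 4.

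If the screening stage is one of the observations, neither problem arises. One sentence thus supports two different primary ORRs, and the choice between them is better fixed in the text than made at analysis.

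**Working it through.** **Planning figures.** Sample size gives 40 analysed per arm and 20% dropout: 40 × 1.20 = 48 per arm, and 2 × 48 = 96, as stated. The allowance is 48 − 40 = 8 patients per arm. The denominator 48 used below assumes that every randomised patient receives a dose.

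**The rule applied to example patients, all alive, with no additional systemic therapy and no day-28 reading.** The non-responder column is the comparator.

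| Readings available | Worst post-baseline category | Screening stage counted | Non-responder imputation |
|---|---|---|---|
| In response on days 4, 8, 15, 22 | responder | non-responder | non-responder |
| In response on days 4 and 8, leaves on day 12 still in PR | responder | non-responder | non-responder |
| In response on day 4 only, then leaves | responder | non-responder | non-responder |
| Unchanged on day 4, in response on days 8, 15, 22 | non-responder | non-responder | non-responder |
| In response on days 4 and 8, back to initial stage on day 15 | non-responder | non-responder | non-responder |
| Leaves before day 4, no exit assessment | no value | non-responder | non-responder |

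The third column follows from the PR definition. If the screening stage is among the observations, the worst one is never better than screening, so it cannot be a one-stage improvement. In the second row, 28 − 12 = 16 days are unobserved.

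**Size.** Let r be the responders observed at day 28 in an arm, m the patients missing at day 28, and q the share of those m with at least one post-baseline reading and every reading in response.

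- Non-responder imputation: ORR = r / 48.
- WOCF over post-baseline readings: ORR = (r + m × q) / 48.
- Difference: m × q / 48. Patients with no value are kept here as non-responders.

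| m | q = 0.10 | q = 0.25 | q = 0.50 |
|---|---|---|---|
| 4 (half the allowance) | 0.8 points | 2.1 | 4.2 |
| 8 (48 − 40) | 1.7 | 4.2 | 8.3 |
| 10 (20% of 48 = 9.6, rounded up) | 2.1 | 5.2 | 10.4 |

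For example, 8 × 0.50 / 48 = 8.3 points. With the screening stage counted, every cell is 0.

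The protocol gives no value for q, so the range is assumed. As a rough guide, suppose 10%, 30% or 50% are in response on day 4 and each later reading stays in response with probability 0.9. The chance that all four readings are in response is then 0.10 × 0.9³ = 0.07, 0.30 × 0.9³ = 0.22, or 0.50 × 0.9³ = 0.36. For those who leave after day 4 alone it is 0.10, 0.30 or 0.50.

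**Between arms.** The treatment difference moves by the difference of the two arms' m × q / 48. It does not move if m × q is equal in both arms.

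**The case against.** The strongest reply is that this is a condensed article which refers to a predetermined analysis plan and a fuller protocol, and that the definition of WOCF may be there. That is fair for the bare lack of detail. It does not settle the point, because the article does state a rule, and on its most natural reading that rule fits a fixed-day binary endpoint poorly.

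Several stronger readings are tempting but not supported:

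- *That WOCF inflates the ORR in general.* It is strict for many missing patients, since any observed non-response makes them failures. It is more lenient than non-responder imputation only for those in response at every observed visit.
- *That the day-4 reading decides the outcome.* Response at the first reading is necessary on the post-baseline reading of the rule, but days 8, 15 and 22 have the same veto. A patient who responds late and then misses day 28 is a failure under the proposed rule too, so that case is no argument for changing it.
- *That everyone who leaves before day 4 has no value.* Death is NR, and an exit evaluation should be attempted. The gap affects only a living patient without that evaluation. If the evaluation is done and shows PR, however, that single early reading would make the patient a responder.
- *That 20% will be missing at day 28.* The allowance carries no timing, follow-up runs to day 360, and the Protocol amendments section describes the subjects as inpatients with dedicated staff. Missingness at day 28 could be much lower.

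It is also fair to say that the trial is declared exploratory and that sampling error is large. At an assumed ORR of 40% in both arms, the standard error of the difference is √(2 × 0.4 × 0.6 / 48) = 0.10, or 10 points.

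**Conclusion.** The point holds in a limited form. Read as the worst post-baseline category, WOCF can credit a day-28 response on early visits alone, and can leave a dosed patient who goes before day 4 without a value if no exit assessment is made. Read with the screening stage included, it equals non-responder imputation. The primary ORR therefore rests on a choice that the article does not state.

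The illustrated shift of 1.7 to 8.3 points in an arm's ORR assumes 8 patients missing at day 28, all 48 in the denominator, and q between 0.10 and 0.50. Halving the number missing halves the shift. It is an illustration, not a forecast, and nothing in the document shows that the arms would be affected unequally. The correction is worth making because it is nearly free and concerns the primary endpoint. The point does not show that the trial's conclusion would be wrong.

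**What to change.** Replace the WOCF sentence with one along these lines: patients in the full analysis set without an aGVHD assessment at day 28 (±1), for any reason, are counted as non-responders in the primary analysis. This gives every patient in the set a value and makes the status of the screening stage irrelevant.

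Keep WOCF as a sensitivity analysis, stating that it runs over post-baseline visits only and how a patient with no such visit is scored. Record each exit assessment under its actual study day, so that an early evaluation made on the visit 19 template is not taken for a day-28 or day-56 result.

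The cost is one sentence, one extra table and possibly a slightly lower ORR. No new data are needed. The change should be fixed before unblinding.

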### Study procedures and assessment

Investigators will introduce the trial to patients, who will be shown video and advertisement sheets describing the main aspects of the trial. Before obtaining informed consent, investigators must provide sufficient explanation to ensure that patients understand the nature, scope, and consequences of the clinical trial.

This trial will include a 7-day screening period, a treatment period lasting 4 to 8 weeks, and a follow-up period. The follow-up will continue until death, withdrawal from the study, or 360 ± 15 days after the first infusion. The flowchart of the study is presented in Fig. 1, and the schedule of screening, intervention. and follow-up are shown in Table 1.

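### Missing values are imputed for day-28 ORR but analysed as observed for every other endpoint, so ORR and CR from one visit get different denominators and ECOG becomes a survivors-only comparison

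*Protocol article*

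**What the plan says.** Two sentences at the end of Statistical analysis set the missing-data rule. The first covers the primary endpoint only: "The missing values of the primary endpoint will be processed by worst observation carried forward (WOCF"). The second covers all the rest: "The other missing values will be analyzed on the actual observed data".

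Study endpoints decides which rule applies to which endpoint:

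- Primary: "The primary endpoint is the overall response rate (ORR) at day 28, which is defined as the proportion of patients achieving a CR or PR", with the further condition that no additional systemic aGVHD therapy was used.
- Secondary: "The secondary endpoints include the CR rate at day 28, ORR at day 56, CR rate at day 56, durable ORR at day 56, DCR," then OS and ECOG. Table 2 gives the times as "OS at day 100, day 180" and "ECOG score at day 28, day 56, day 100".

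Table 2 also settles the status of death on the response scale: "No response (NR): the absence of improvement or deterioration of symptoms in any organ or death".

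Statistical analysis puts both primary and secondary efficacy on the FAS (described as following the ITT principle, with at least one dose received) and on the PPS. Under Study procedures and assessment, "The follow-up will continue until death, withdrawal from the study" or about day 360, so a patient who withdraws has no scheduled assessments afterwards. Investigators are asked to try to complete the visit-19 (day-56) evaluation before a patient leaves.

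**The concern.** Day-28 ORR and day-28 CR are read from the same aGVHD evaluation at the same visit, and CR is a subset of ORR. Under the stated rules, a living patient with no day-28 evaluation is imputed for one and omitted from the other. The two rates then describe different sets of patients and can appear in an order that is logically impossible.

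Beyond day 28, the observed-data rule shrinks an ITT-based FAS to the patients who were assessed. If the unassessed patients are mostly non-responders, the secondary response rates are too high. If the number unassessed differs between arms, a treatment difference can appear or be distorted with no real cause. For ECOG the article gives no value for a patient who has died, so the comparison at days 28, 56 and 100 is restricted to survivors still in the study. That set is defined after randomisation.

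**Working it through.** **Inputs.** Sample size gives 40 analysed per arm, a 20% dropout allowance and 48 enrolled per arm. The article states no response rates, missing counts or splits between arms, so all of those below are assumptions. All 48 per arm are taken as dosed and hence in the FAS.

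**The plan's own figure.** 40 × 1.20 = 48 per arm and 2 × 48 = 96, as stated. The gap is 48 − 40 = 8 patients per arm (8/48 = 16.7%). I use 8 as the central missing count and 5 to 10 as a range. The missing patients are alive, have no assessment, and are non-responders under WOCF.

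**1. Inflation of one rate.** With *c* complete responders and *m* missing, the FAS rate is *c*/48 and the observed rate is *c*/(48 − *m*).

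| c | m | FAS rate | Observed rate | Difference (points) |
|---|---|---|---|---|
| 10 | 5 | 10/48 = 20.8% | 10/43 = 23.3% | 2.4 |
| 16 | 8 | 16/48 = 33.3% | 16/40 = 40.0% | 6.7 |
| 20 | 10 | 20/48 = 41.7% | 20/38 = 52.6% | 11.0 |

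**2. CR above ORR.** With *R* responders, ORR is *R*/48 and CR is *c*/(48 − *m*). CR exceeds ORR when *c*/*R* > (48 − *m*)/48, which for *m* = 8 is 40/48 = 83.3%. Take *R* = 22, so ORR = 22/48 = 45.8%:

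- *c* = 22: CR = 22/40 = 55.0%.
- *c* = 19: CR = 19/40 = 47.5%, still above ORR.
- *c* = 18: CR = 18/40 = 45.0%, below ORR.

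The reversal therefore needs most responders to be complete. The mismatch in denominators does not.

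**3. Unequal missingness between arms** (Pearson chi-square, no continuity correction).

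| CRs per arm | Missing per arm | FAS | Observed |
|---|---|---|---|
| 16 v 16 | 12 v 4 | 33.3% v 33.3% | 16/36 = 44.4% v 16/44 = 36.4%, p = 0.46 |
| 18 v 14 | 12 v 4 | 37.5% v 29.2%, p = 0.39 | 18/36 = 50.0% v 14/44 = 31.8%, p = 0.10 |

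In the first row an 8.1-point difference appears where the FAS has none. In the second, an 8.3-point difference becomes 18.2 points.

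**4. Who leaves which endpoint under the text as written.**

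| Endpoint | Living patient, no assessment | Death |
|---|---|---|
| ORR day 28 | kept, by WOCF | kept, as NR |
| CR day 28; ORR and CR day 56 | leaves | kept, as NR |
| Durable ORR day 56 | leaves unless already a failure (for example NR or PD at day 28) | kept, as NR |
| DCR | leaves unless failure is already established | best read as failure if 28 days of CR had not been reached; not stated |
| ECOG days 28, 56, 100 | leaves | leaves |

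**The case against.** Several stronger readings are tempting, and the article does not support them.

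- **Deaths vanish from response and OS.** They do not. Table 2 makes death a form of NR, which is an observed category, and in OS death is the event. Only ECOG loses the dead.
- **Patients lost before day 100 or 180 are discarded from OS.** A reader might infer this from the observed-data sentence and the fixed time points. However, the article names no survival method, and both features are compatible with a Kaplan-Meier curve that censors at last contact and is read at those days. The SAP may settle this.
- **WOCF fails for the primary endpoint.** A patient with PR at every attended visit might be carried forward as a responder, or might have nothing to carry. That depends on whether the screening evaluation counts as an observation, which is also a detail the SAP may hold.
- **Dropout concentrates in non-responders because treatment stops at day 28 for NR and PD.** Trial design stops it for CR as well. Stopping infusions is also not leaving the study: the notes to Table 1 keep patients who deviate from the intervention on the same assessment calendar.

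The amount of missing data may also be small. Patients are inpatients with dedicated follow-up staff, a visit-19 evaluation is attempted before withdrawal, and the 20% is a sample-size allowance, not a forecast of missing evaluations. If the unassessed would have responded at the same rate as the assessed, observed-data rates are not biased. The affected endpoints are secondary, in a trial that calls itself exploratory.

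These points limit the scope and likely size. They leave standing the two rules for one day-28 evaluation, the loss of unassessed patients from the FAS, and the gap for ECOG. The visit-19 provision helps only in part: it is best effort, and the article does not say whether an early evaluation serves as the day-28 or day-56 value.

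**Conclusion.** The point holds in a limited form. The article itself fixes a rule that gives day-28 ORR and day-28 CR different denominators and removes living, unassessed patients from the secondary response endpoints, against the ITT-based FAS named for them. ECOG additionally loses the dead.

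Under the assumed 5 to 10 missing per arm and 10 to 20 complete responders, the CR rate rises by 2.4 to 11.0 points. At 8 missing, CR passes ORR once more than 83.3% of responders are complete. The upward direction rests on the missing being mostly non-responders, which is plausible but not shown. The between-arm distortions rest on an assumed 12 v 4 split, and none of those illustrative comparisons reaches p < 0.05.

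This should be fixed, but it is not an obstacle to the trial: the primary endpoint has its own imputation rule and is unaffected. No conclusion is drawn about the OS method or about WOCF.

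**What to change.** Before unblinding, replace the observed-data rule for the secondary endpoints with the following:

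1. For CR at days 28 and 56, ORR at day 56, durable ORR and DCR, count any FAS patient without the required assessment as a non-responder, with the full FAS as denominator. Day-28 CR then has the same denominator as the primary endpoint and cannot exceed ORR.
2. For ECOG at days 28, 56 and 100, rank death as the worst category in the Wilcoxon comparison.
3. Keep observed-case results for all of these as sensitivity analyses, and report the number unassessed by arm and visit.

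The cost is a few sentences of wording and minor programming on data already being collected. Reported response rates will be slightly lower, and conservative if some unassessed patients had in fact responded. The observed-case results will show how much that matters.
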